### Concealment mechanism {16b}

This is not applicable as the study is single-blind. It is only the patient who is not informed of the imaging technique used; the surgeon is informed.

### Implementation {16c}

Patients are randomized 1 day before surgery using a computer-generated allocation list (generated using R version 4.1.3). The randomization list is linked to the study’s data management program (REDCap) by the project statistician. The operating surgeon recruits the patients and collects the data needed to conduct the study. The day before surgery, the surgeon enters the data into the electronic case report form (eCRF) in REDCap, which is designed for this study. Once the patient is enrolled in the study and the required data is entered into the system, the patient is automatically assigned to an intervention group using the linked randomization list. This ensures that surgeons have no influence on patient allocation. However, they are unblinded and are informed on the preoperative day which laparoscopic system will be used for the next surgery in the study. This is unavoidable, which is why our study is single-blind. Only the patients are blinded.

## Assignment of interventions: blinding

### Who will be blinded {17a}

The study is single-blind. The patients are blinded, and they do not know which group they belong to, while the investigators are not blinded. The blinding of the patients is ensured by the fact that there is no visible difference between the two groups, as well as by standardized questions and discussion patterns of the investigators, so that no relevant information is revealed. Whether the laparoscopic surgery is performed with 2D 4K or 3D HD imaging is irrelevant for the preoperative assessment and the subsequent procedure. This also applies to the follow-up procedure.

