Role of sponsor {5c}	[name] is the Sponsor-Investigator and one of the operating surgeons in the study. Together with his surgical team, he will recruit patients, inform them about the study and obtain informed consent. He will be responsible for performing the surgeries and collecting the data. After surgery, he will provide the data to the other authors of the study for further processing, analysis, and interpretation, and will write the report. He has final authority over all activities.

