#### Secondary

Secondary outcomes include intraoperative complications, operator workload, and postoperative complications. Intraoperative complications are assessed descriptively by the surgeon’s documentation in the operative report. These include major bleeding, injuries or burns to surrounding organs (e.g., stomach, esophagus, spleen, liver), circulatory problems, or unexpected intra-abdominal findings that deviate from the standardized surgical procedure or expected extent and must be noted in the operative report. Blood loss is recorded and documented quantitatively in milliliters. In addition, a postoperative Hb control is performed if indicated by intraoperative complications and the Hb decrease is determined. Immediately after each surgery, the surgeon completes the Surg-TLX questionnaire, a validated multidimensional measure of surgical workload. The Surg-TLX defines workload based on six dimensions: mental demands, physical demands, temporal demands, task complexity, situational stress, and distractions. The condition of the operating surgeon has a great influence on the outcome of an operation. Especially when using 3D imaging, some undesirable side effects have been reported. It is important to determine the subjective workload of the surgeon when using modern imaging and performing a more complex procedure. Postoperative complications are influenced by many factors, including operative time and intraoperative complications. It is important to capture these in order to compare the postoperative outcomes of the two imaging systems. Postoperative complications are classified and documented up to 90 days according to the internationally accepted Clavien-Dindo classification. In addition, the length of hospital stay is evaluated. The standard length of hospital stay is three nights or 4 days, defined from the day of surgery, which is also the day of admission, up to and including the day of discharge. Other outcomes of interest are confounding parameters that we will consider in the statistical analysis. These include age, sex, and BMI of the operated patients. Another possible parameter, if available, is the number of previous abdominal surgeries a patient has had. Previous abdominal surgeries, especially upper abdominal surgeries, may be a complicating factor and will be reported and considered accordingly. Furthermore, it is documented exactly which operation was performed by which of the three surgeons as well as their personal prevalence (2D 4K vs. 3D HD). This is to analyze a possible bias.

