## Oversight and monitoring

### Composition of the coordinating center and trial steering committee {5d}

This is a monocentric study designed, conducted, and coordinated at the University Hospital of Basel. The day-to-day management of the study is carried out by the following:Sponsor-investigator: takes over the supervision of the study and the medical responsibility for the patients, in addition he is one of the three defined operators of the studyMedical expert: advises, conducted the corresponding preclinical study comparing 2D 4K vs. 3D HD on a pelvitrainer model [8]Study coordinator: enrollment, coordination of study visits, annual safety reportsStatistician: organizes data collection, ensures quality, and analyzes dataOther investigators/operators: recruit, obtain consent, operate, and ensure follow-up according to protocol

The study team meets as needed, but not regularly. There is no study steering committee or stakeholder/public engagement group.

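### The exploratory 90-day Clavien-Dindo comparison is graded by a team that knows the arm, for a reason that covers only the operating surgeon

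*Protocol article*

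**What the plan says.** All of the following is in the protocol article.

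- **Who is blinded.** On the patients, Who will be blinded {17a} says "they do not know which group they belong to, while the investigators are not blinded". Implementation {16c} adds: "Only the patients are blinded".
- **Why.** Implementation {16c} explains that surgeons learn on the day before surgery which system they will use, and concludes: "This is unavoidable, which is why our study is single-blind".
- **Who handles data and follow-up.** Implementation {16c}: "The operating surgeon recruits the patients and collects the data needed to conduct the study". Role of sponsor {5c} says of the sponsor-investigator, who is one of the operators: "He will be responsible for performing the surgeries and collecting the data". The committee section {5d} gives the other investigators/operators the task to "recruit, obtain consent, operate, and ensure follow-up according to protocol".
- **The outcome.** Outcomes {12}, Secondary: "Postoperative complications are classified and documented up to 90 days according to the internationally accepted Clavien-Dindo classification". Plans for assessment and collection of outcomes {18a} repeats this. Neither section names the person who assigns the grade.
- **How it is analysed.** Statistical methods {20a} treats every parameter other than operating time as secondary and compares these parameters in an exploratory way, two-tailed at 0.05.
- **Follow-up and imaging.** Section {17a} says that the choice of imaging has no bearing on preoperative assessment or later care, including follow-up.
- **Other team members.** Section {5d} also lists a study coordinator, a medical expert and a statistician. None of them is described as an operator.

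**The concern.** The operating surgeon cannot be masked to the imaging system. Operating time and the surgeon's own Surg-TLX rating share that limit. A Clavien-Dindo grade assigned up to 90 days later does not. It can be read from the discharge letter, readmission records and the 3-month visit note by someone who does not know which camera was used.

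The article nevertheless applies one blinding statement to everything, and its justification fits only the operation. The trial has a stated directional hypothesis (Objectives {7}), and its Strengths section anticipates better patient outcomes if 3D HD shortens surgery. Low-grade calls need judgement, for example whether a deviation is grade I, grade II or ordinary recovery. Knowledge of the arm could influence such calls. What is at stake is how far readers can trust the complication comparison, which Objectives {7} presents as part of a comprehensive overview of the two systems.

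**Working it through.** **1. Does the text exclude a masked grader?** Yes. Sections {16c} and {17a} say that patients alone are blinded and that the investigators are not. This is a stated design choice, so it is not a detail that an article leaves to the full protocol.

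**2. Does the stated reason cover 90-day grading?** Set side by side:

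| Assessment | Must the assessor know the arm? | Covered by the reason in {16c}? |
|---|---|---|
| Operation and operating time | Yes, the surgeon uses the system | Yes |
| Surg-TLX | Yes, the surgeon rates the operation just done | Yes |
| Clavien-Dindo grade to 90 days | No, {17a} says imaging does not affect follow-up | No |

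The article gives no other reason for unblinded grading.

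**3. Do other safeguards fill the gap?** No.
- The standardized questioning in {17a} protects the patients' blinding.
- Monitoring with source data verification ({23}) compares entries with the source and does not regrade them.
- Data management {19} has authorized personnel transfer the data. They are not described as masked, and {16c} rules that out.
- There is no data monitoring committee ({21a}).

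**4. How sensitive is the comparison?** The article states no figure on this point, so there is none to reproduce. Inputs: 48 patients (Sample size {14}) allocated 1:1 (Trial design {8}), so 48/2 = 24 per arm.

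- One changed call moves that arm's rate by 1/24 = 4.2 percentage points.
- One call in each arm, in opposite directions, moves the difference by 2/24 = 8.3 points.

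These figures follow from the arm size alone and would hold for any binary outcome here. Two-sided Fisher tests with 24 per arm, starting from equal counts and moving one call each way:

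| Counts | p |
|---|---|
| 1 vs 3 | 0.61 |
| 3 vs 5 | 0.70 |
| 5 vs 7 | 0.74 |

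Reaching p < 0.05 takes a split such as 0 vs 5 (p = 0.0496) or 1 vs 7 (p = 0.048).

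**5. Illustration under assumptions.** The article gives neither a complication rate nor the size of an assessor effect. Assume no true difference, a true risk p of 10 to 30% in both arms, and a relative under-recording r in one arm. The recorded risk in that arm is p(1 − r), so the spurious difference is p × r. The chance of Fisher p < 0.05 is the sum of the two binomial probabilities over all count pairs that reach it.

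| True risk | r = 0 | r = 25% | r = 50% |
|---|---|---|---|
| 10% | 1.7% | 1.8% (2.5 points) | 2.8% (5 points) |
| 20% | 2.6% | 4.0% (5 points) | 9.7% (10 points) |
| 30% | 2.6% | 5.3% (7.5 points) | 16.1% (15 points) |

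Each cell gives the chance of p < 0.05, with the spurious difference in brackets. At 25% under-recording, false significance stays near or below the nominal 5%. It clearly exceeds 5% only at 50% under-recording with a risk of 20% or more. The estimated difference is distorted in every biased case.

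**The case against.** **A stronger reading is tempting, and the article does not support it.** A reader might infer that each surgeon grades complications in his or her own patients. No section says so. The outcome sections use the passive, and the sentence about data collection in {16c} stands beside the entry of preoperative data. Sections {18a}, {19} and {5d} also point to shared data handling. A reader might also infer that a few calls would decide a safety comparison. That fails too: the comparison is exploratory, the hypothesis concerns operating time, no formal safety claim is planned, and one changed call per arm comes nowhere near significance.

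**Section {17a} is about care.** Its remark on imaging and follow-up explains why patients stay blinded. Unblinded grading does not contradict it. This stands. The remark shows only that follow-up does not need the arm to be known.

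**Masked grading is a partial remedy.** If surgeons still detect and record the events, an event never written down cannot be recovered. This stands and has to be declared as a limitation.

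**The candidate graders are not ideal.** The medical expert conducted the preclinical study behind the hypothesis and takes part in the interim discussion. Prior belief does no harm if the grader does not know the patient's arm. For the coordinator the objection has more force, because enrollment and safety-report duties may reveal the allocation.

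**Single-blinding is openly declared.** This is true, but the declaration gives a reason for the operation only.

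**Conclusion.** The point holds as a modest design weakness. Sections {16c} and {17a} exclude masked grading of the 90-day complications, and the only reason given applies to the operating surgeon. This follows from the text and needs no assumption about who grades.

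Its size is not known. The 4.2 and 8.3 points describe how coarse a 24-per-arm comparison is. The spurious differences of 2.5 to 15 points rest on assumed risks and assumed under-recording. Neither the size nor the direction of an actual bias can be taken from the article.

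The primary test of operating time is untouched. Because the outcome is secondary and exploratory, and the remedy covers grading but not detection, this is a change to consider and not a condition for the trial's validity.

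**What to change.** - Leave clinical follow-up, recording of events and judgement of device-relatedness with the surgeons.
- Have the Clavien-Dindo grade used in the analysis assigned by an existing non-operating team member who is masked at patient level. Hide the allocation field in REDCap from that person, and remove the imaging system from the discharge letter, readmission records and 3-month note. The coordinator suits only if enrollment and safety-report duties do not reveal the arm.
- In Implementation {16c}, limit the claim that unblinding cannot be avoided to the operation, operating time and Surg-TLX, and align {17a} with it.
- Add to Limitations that detection and recording of complications remain unblinded.

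**Cost:** a REDCap access setting, light redaction and a few minutes per patient for 48 patients. Sample size, alpha, power and patient care do not change.

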### Procedure for unblinding if needed {17b}

This is not applicable; there is no situation that would require unblinding the patient.

## Data collection and management

### Plans for assessment and collection of outcomes {18a}

Data will be derived from electronic patient records and collected with an electronic case report form (eCRF) using REDCap electronic data capture tools hosted at the University of Basel. REDCap (Research Electronic Data Capture) is a secure, web-based software platform designed to support data collection for research studies [22, 23]. Laboratory testing is a standard part of the gastric bypass procedure and is performed in the central diagnostic laboratory of the University Hospital of Basel. The operative reports and other relevant information will be collected from the electronic patient records in the internal system of the University Hospital of Basel, and the information relevant to the study will be extracted and collected in the eCRF and in a folder created for the study. Only the study team has access to this specific study folder. The SURG-TLX is used to measure the surgeon’s workload immediately after surgery. The Surgery Task Load Index (SURG-TLX) is a validated multidimensional workload measure. It is a surgery-specific adaptation of the well-validated NASA-TLX and was proposed by Wilson et al. to assess the sources of workload perceived by surgeons in the operating room environment [24]. It has been used in robotic surgery in clinical settings and has been suggested to be useful in assessing human-machine interface issues and sources of stress caused by new technology in surgical practice. The questionnaire assesses operator workload along six dimensions:Mental demands: How mentally fatiguing was the procedure?Physical demands: How physically fatiguing was the procedure?Temporal demands: How hurried or rushed was the pace of the procedure?Task complexity: How complex was the procedure?Situational stress: How anxious did you feel while performing the procedure?Distractions: How distracting was the operating environment?

Postoperative complications are documented until 90 days postoperatively. Postoperative complications are classified into grades I–V according to the widely used and internationally accepted Clavien-Dindo classification [25].

### Plans to promote participant retention and complete follow-up {18b}

This is not applicable because the procedure and study follow-up (up to 90 days post-operatively) are performed as part of the standard gastric bypass procedure. In order to receive the gastric bypass indication, patients must sign a written consent for lifelong follow-up in the bariatric network at a certified center. This is in accordance with standard guidelines.

### Data management {19}

All source data are available at the University Hospital Basel. The source data include the original documents related to the study (signed informed consent, randomization codes) and the patient information contained in the electronic system of the University Hospital Basel. This includes the patient’s general data, medical history, and collected medical parameters (laboratory) as well as the operative reports and documented progress notes. All this data is stored in the internal system, to which authorized personnel have access. Data relevant to the primary and secondary outcomes are selectively transferred into REDCap by authorized personnel and collected in a GCP-compliant eCRF. The system allows for minimizing data entry errors through the development of branching logic and online data checks (e.g., range checks). Relevant documents such as the signed informed consent and operative report are also stored there. The operator workload questionnaire is completed directly online in the eCRF. In addition, (S)AEs are recorded in the eCRF.

Data will be exported by REDCap in CSV format and evaluated by the project statistician at interim and final analysis. The entire database will be exported at the end of the study and stored in the archives of the University Hospital Basel for a minimum of 10 years after the study has been terminated.

### Confidentiality {27}

Data entry and analysis will be done with anonymized data. Research data will be stored in the eCRF using a study identification code for each participant. The key to the list of identification codes will only be available to the research team during the study. Patient identification details will not be reported in publications.

### Plans for collection, laboratory evaluation, and storage of biological specimens for genetic or molecular analysis in this trial/future use {33}

This is not applicable; there was no collection of biological specimens.

## Statistical methods

### Statistical methods for primary and secondary outcomes {20a}

Data will be analyzed using rpact (R package version 3.2.1) [21]. Descriptive statistics of primary and secondary endpoints will include minimum, maximum, standard deviation, mean, median, interquartile, 25th percentile, and 75th percentile for each study group.

The primary endpoint (mean OT) will be compared between study groups using an independent *t*-test. Since the distribution of OT is expected to be approximately symmetric with no outliers, the *t*-test is the primary choice. The tests will be one-tailed at a 2.5% significance level. Based on the O’Brian-Fleming alpha power function, the critical *p*-value is 0.0015 at the interim analysis and 0.0245 at the final analysis. Stop for futility is non-binding and set > 0. Acceptance of H1 will be concluded if alpha < critical values at the appropriate stages.

Study parameters other than OT are considered secondary. Secondary endpoints will be compared exploratorily using Mann-Whitney *U*-tests or Fisher’s exact tests, as appropriate. Tests will be two-tailed, alpha = 0.05.

Study groups will be exploratorily adjusted for age, sex, BMI, and possibly other parameters using regression analysis.

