### Sample size {14}

The sample size was calculated for the primary outcome (operating time). As the study is mainly based on knowledge from preclinical studies and there is not much guiding literature in the clinic, some assumptions had to be made at the beginning. We assume that an operator needs approximately 75 min to perform a gastric bypass using 3D HD imaging, while performing the exact same operation using 2D 4K imaging takes 90 min. This assumption is supported by the literature, which states that a gastric bypass operation takes approximately 90 min for experienced operators using 2D laparoscopy, by the results of studies that showed a time savings of approximately 15 min using 3D laparoscopy, and by the results of our preliminary study, which showed an average time savings of almost one fifth using 3D laparoscopy compared to 2D 4K [18–20]. The EAES systematic review also suggests an average difference of 15 min for procedures involving laparoscopic suturing [2]. Calculation is as follows: sequential analysis with a maximum of 2 looks (group sequential design, O’Brian-Fleming alpha spending), overall significance level 2.5% (one-sided); the sample size was calculated for a two-sample *t*-test, minimal detectable difference = 15, standard deviation = 15, power 90%; futility bound of 0 at interim analysis; number of subjects at interim 22.3, final: 44.6. Sample size calculation is based on RPACT (R package version 3.2.1) [21].

Therefore, we will recruit 48 patients in blocks of four with gastric bypass indications and randomize them to the two groups (2D 4K and 3D HD).

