## Assignment of interventions: allocation

### Sequence generation {16a}

Patients are randomly assigned to the four possible sequences using block randomization with a block size of four patients. The two groups will be assigned according to the randomization list, and surgery will be performed based on these groups using either 2D 4K or 3D HD imaging. If a patient fails to complete the study, the next patients will follow the list at the same point as the failed patient. There is no prior stratification.

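### The primary t-test leaves out surgeon, although three surgeons do every operation; adding it is a cheap gain in precision if surgeons differ, not the repair of an error

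*Protocol article*

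**What the plan says.** The section on statistical methods for primary and secondary outcomes {20a} states: "The primary endpoint (mean OT) will be compared between study groups using an independent" t-test, one-tailed, with critical p-values of 0.0015 at the interim and 0.0245 at the final analysis. No covariate enters that test.

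The study setting {9} and intervention description {11a} assign all operations to three named senior surgeons. Under secondary outcomes {12}, "it is documented exactly which operation was performed by which of the three surgeons", together with each surgeon's preferred system, and the stated reason is to examine possible bias. Sequence generation {16a} uses blocks of four and adds: "There is no prior stratification".

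The only adjustment is exploratory: "Study groups will be exploratorily adjusted for age, sex, BMI, and possibly other parameters using regression analysis". Surgeon is not among the named covariates, but the last clause does not exclude it.

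**The concern.** Operating time can depend on who operates. Blocks of four keep the arms equal overall, but not within each surgeon's cases. If the three surgeons differ in speed, the t-test has two costs. It counts between-surgeon variation as noise, and any unequal surgeon mix between the arms stays in the primary estimate. The variable that would deal with both is already collected for every patient, and the protocol itself treats it as a possible source of bias.

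At stake are some power and the credibility of the estimate if the surgeon mix turns out uneven. A surgeon adjustment chosen after the results are known would carry little weight.

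**Working it through.** **Inputs from the protocol.** Sample size {14}: "overall significance level 2.5% (one-sided"), "sequential analysis with a maximum of 2 looks", "minimal detectable difference = 15, standard deviation = 15, power 90"%, "futility bound of 0 at interim analysis"; 48 patients, 1:1, blocks of four. Critical p-values 0.0015 and 0.0245.

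**Input not in the protocol.** The difference between surgeons. I assume surgeon means of -m/0/+m min and show m = 0, 4, 8 and 12, with each patient equally likely to have any of the three surgeons.

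**1. The plan's own figures.** The fixed-design total for a one-sided t-test (alpha 0.025, power 90%, difference/SD = 1) is 44.04. The two-look inflation factor is 1.0116, and 44.04 × 1.0116 = 44.55, half of which is 22.3. The stated 44.6 and 22.3 reproduce, as do the critical p-values (0.00153 and 0.02450).

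**2. Power of the planned t-test at 48 patients, final look.** Noncentrality = (15/15) × √(48/4) = 3.46 on 46 df, which gives 92.2% at one-sided 0.0245. The planned power is met.

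**3. Type I error.** In simulation (12 blocks of four, surgeon drawn at random), the t-test rejected a true null in about 2.1% to 2.8% of trials against a nominal 2.45%, the same as the adjusted model within simulation error.

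**4. How often the surgeon mix is uneven.** Some surgeon's cases differ by 4 or more between arms in 53% of trials, and by 6 or more in 21%. These are counts of cases; step 5 turns them into minutes.

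**5. Shift in the unadjusted estimate.** Between-surgeon variance = 2m²/3. SD of the shift = √[(2m²/3) × (1/24 + 1/24)], and 5% of trials exceed about 1.96 times that.
- m = 4: variance 10.67, SD 0.94, limit about 1.8 min
- m = 8: variance 42.67, SD 1.89, limit about 3.7 min
- m = 12: variance 96, SD 2.83, limit about 5.5 min

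The target difference is 15 min.

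**6. Power if 15 is the total SD.** The within-surgeon SD is √(225 − 2m²/3), that is 15.0, 14.6, 13.5 and 11.4. Simulated power, t-test (46 df) against model with surgeon (44 df), one-sided 0.0245:

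| Surgeon means | Effect 15 min | Effect 10 min |
|---|---|---|
| equal | about -1 point | about -1.5 to -2 points |
| -4/0/+4 | about 0 | about +1 point at most |
| -8/0/+8 | 92% to 96% | about 61% to 68% |
| -12/0/+12 | 92% to 99% | about 62% to 83% |

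An uneven caseload of 60/25/15% gave nearly the same results when surgeon explained 10% to 50% of the variance.

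**7. Power if 15 is the within-surgeon SD.** The total SD is then √(225 + 2m²/3).
- m = 4: 15.4, about 91% for both analyses
- m = 8: 16.4, t-test about 87%, adjusted about 91%
- m = 12: 17.9, t-test about 80 to 81%, adjusted about 91%

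**The case against.** The case for leaving the plan alone is substantial. The t-test is valid, it is the test used to size the trial, and on the natural reading of the sample-size section (15 as the SD in a two-sample t-test) it exceeds the planned power. Over repeated randomisations surgeon imbalance adds variance that the t-test's error term already covers; it is not systematic bias. The three surgeons are described as senior and experienced with both systems, and the operation as highly standardised. They may therefore differ little, and at ±4 min there is nothing worth gaining. The protocol also has a route for surgeon through the open clause of the exploratory regression, and the full covariate list may sit in an analysis plan that is not shown.

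All of that stands, and it rules out three stronger readings that a reader might infer:
- That precision is certainly lost. No between-surgeon variance is given, and if surgeons are equal, adjusting costs a little.
- That the trial is underpowered. This needs 15 to exclude surgeon variation, which the protocol does not say, together with differences larger than ±4.
- That surgeon is ignored altogether. It is recorded with a stated purpose and is not excluded from the exploratory model.

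What the objection does not remove is that the confirmatory analysis is fixed without a variable the protocol itself flags, and that an unspecified exploratory adjustment cannot substitute for a prespecified one.

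**Conclusion.** A worthwhile improvement, not an error. The plan's sample size, critical values and type I error all hold. Within ±12 min, prespecifying surgeon costs at most about 1 point of power at a 15 min effect, or 2 points at 10 min, and gains up to 7 points at 15 min (92% to 99%) or about 21 at 10 min (62% to 83%). It also removes a chance shift that reaches at least 3.7 min in 5% of trials at ±8 and 5.5 min at ±12.

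The 10 min column matters because the protocol's introduction reports that both cited clinical comparisons of 3D with 4K found no reduction in operating time, so an effect below 15 min is plausible.

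The textual facts are certain; the size of the benefit is not. It rests on assumed surgeon means, roughly even caseloads and power taken at the final look only.

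**What to change.** By amendment, before anyone sees an unblinded comparison of the arms (so before the interim analysis), define the primary analysis as a linear model of operating time on arm with surgeon as a fixed effect. Test the arm coefficient one-sided against the same critical p-values, 0.0015 and 0.0245. Keep the t-test as a sensitivity analysis.

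Use the surgeon assigned before allocation, so that a change of operator after the system is known cannot affect the covariate. Under implementation {16c} the operating surgeon recruits the patient and enters the data that trigger allocation, so this information should be available. BMI may be added, but nothing calculated here supports or opposes it.

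The cost is two degrees of freedom, about 1 to 2 points of power if surgeons do not differ, and an ethics committee submission, since recruitment began in August 2023 and a change to the primary analysis is more than an edit. No new data are needed.
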